## Abstract

**Background:**

Australian Aboriginal children experience high levels of dental caries (tooth decay) and are less likely to access preventive dental health services. High-strength fluoride varnish has been shown to reduce the incidence of dental caries and is commonly used in community-based preventive dental health service programs. In New South Wales, Australia, the application of fluoride varnish is restricted to dental and medical professionals. This is problematic in communities with a high Aboriginal population and limited access to oral health services, contributing to the increased risk of developing dental caries in Aboriginal children. Dental assistants are essential members of the oral health team; however, they do not have a defined scope of practice in Australia. Other countries have created formal scopes of practice for dental assistants to include the application of fluoride varnish. This protocol presents a pathway for qualified Aboriginal dental assistants to undertake additional training to legally apply fluoride varnish in New South Wales. The primary objective of this study will be to evaluate the feasibility and acceptability of utilising Aboriginal dental assistants to apply fluoride varnish to Aboriginal children in a school setting at regular 3-month intervals.

**Methods:**

Six schools across New South Wales (NSW) that enrol at least 12% Aboriginal children will be invited to participate in the 12-month study. Aboriginal children aged 5–12 years enrolled in these schools will be enrolled in the study. Six Aboriginal dental assistants will undertake training to apply fluoride varnish. Fluoride varnish (Duraphat) will be applied at 3-month intervals by the dental assistants to the teeth using a small brush. An evaluation will be undertaken to determine the feasibility and cost-effectiveness of this innovative approach. This study protocol has been approved by the NSW Aboriginal Health and Medical Research Council and the NSW State Education Research Application Process.

**Discussion:**

A qualified Aboriginal dental assistant workforce in NSW (or Australia) legally approved to apply fluoride varnish may increase the sustainability and scalability of fluoride varnish programs and improve the oral health of Aboriginal children in Australia.

**Trial registration:**

ISRCTN26746753.

**Electronic supplementary material:**

The online version of this article (10.1186/s40814-019-0399-4) contains supplementary material, which is available to authorized users.

## Background

Dental caries (tooth decay) is a widespread chronic disease among Australian children which is largely preventable [1, 2]. Australian Aboriginal children experience higher levels of dental caries than non-Aboriginal children. In New South Wales (NSW) for example, Aboriginal children experience 2.64 teeth on average affected by dental caries, compared to 1.54 teeth for non-Aboriginal children [3]. Untreated dental caries can cause considerable pain, impacting on a child’s school attendance, ability to chew or speak normally and overall quality of life [4].

Varnishes which contain higher levels of fluoride were developed in the 1960s to prevent dental caries [5]. They are safe [6] and widely used internationally in community-based preventive dental health service programs [7]. A meta-analysis of clinical trials undertaken by the Cochrane review aimed to assess the caries preventive effect of fluoride varnish concluded that fluoride varnish applied to the teeth two to four times per year is associated with a substantial reduction in caries development [7]. This included a 43% reduction in decayed, missing and filled tooth surfaces in the permanent dentition and 37% reduction in the primary dentition.

Under current Australian legislation (with exception to the Northern Territory), only medical and dental professionals can apply fluoride varnish [8]. Due to the uneven supply of oral health professionals in rural areas [9, 10], there is limited access to evidence-based preventive dental health services in rural and remote communities with high Aboriginal populations. This contributes to the complex matrix of risk factors for the development of dental caries in Aboriginal children. In NSW, a pathway exists to allow non-medical or dental professionals to apply fluoride varnish following approval from the Chief Health Officer [11].

In the Northern Territory, non-dental professionals including Aboriginal Health Workers, Aboriginal Health Practitioners and school or child health nurses are legally able to apply fluoride varnish, following mandatory training [12]. This initiative assists in improving access to preventive services for Aboriginal children. Improving the oral health of priority populations including Aboriginal people is documented in Australia’s National Oral Health Plan. The plan also strongly supports the expansion of fluoride varnish programs and seeks greater uniformity of Australian legislation to support fluoride varnish programs which may improve oral health of priority populations [13]. Furthermore, the NSW State Government has developed a set of guidelines to increase access to fluoride for target populations in NSW. These include the implementation of community fluoride varnish programs [14].

Dental assistants are essential members of the oral health team. Whilst they are not regulated by the Dental Board of Australia and as such do not have a defined scope of practice, in NSW, Victoria and South Australia, dental assistants are included in legislative frameworks that impose standards on non-registered health practitioners who are involved in the provision of health services [15]. In Australia, vocational training is available for dental assistants to become qualified. This training is administered and delivered through a Registered Training Organisation with an approved curriculum that includes cross-infection control and dental anatomy, both of which are relevant to the application of fluoride varnish.

Other countries have created formal scopes of practice for dental assistants to include the application of fluoride varnish [16, 17]. In the UK, for example, the General Dental Council allows trained and competent dental nurses to apply fluoride varnish direct in community-based fluoride varnish programs and under the direction of a dentist in practices. Eighty percent of these dental nurses expressed they were confident applying fluoride varnish [17]. In Scotland, as part of the Childsmile program, Extended Duties Dental Nurses (EDDNs) provide fluoride varnish applications to preschool children. The EDDNs showed professionalism when working with children, and no incidents had been reported [16].

A small-scale study in Central Northern NSW, Australia, used oral health therapists to deliver 3-monthly applications of fluoride varnish to Aboriginal school children [18]. The study provided at least three fluoride varnish applications for Aboriginal children over a 12-month period and noted that such an approach could be modified to use dental assistants to increase the sustainability of the program [18]. The proposed pilot project will enable dental assistants to apply fluoride varnish as an alternative to oral health professionals and may increase the sustainability and scalability and reduce the costs of fluoride varnish programs. This approach may also increase access to evidence-based preventive dentistry for Aboriginal children living in communities with limited dental services.

This study protocol presents a pathway for qualified Aboriginal dental assistants to undertake additional training to legally apply fluoride varnish in NSW. The primary objective of this 12-month, single group study across seven schools will be to test the feasibility and acceptability of Aboriginal dental assistants applying fluoride varnish in a school setting for children at risk of dental caries. Secondary objectives of this study are as follows:To determine the feasibility of utilising Aboriginal dental assistants to apply fluoride varnish at regular 3-month intervalsTo determine whether this model can provide Aboriginal children with at least three applications of fluoride varnish over the 12-month study periodTo explore the confidence of dental assistants applying fluoride varnishTo explore the acceptability of using dental assistants to deliver fluoride varnish in the school settingTo determine the cost-effectiveness of utilising dental assistants to provide four fluoride varnish applications in the school setting over the 12-month study period compared to oral health therapists

## Methods

### Setting

Aboriginal Community Controlled Health Services are health care services that are operated by the local Aboriginal community. They deliver holistic, culturally competent health care to the local Aboriginal community and liaise with local organisations such as schools on issues affecting the health and well-being of Aboriginal people [19]. Six Aboriginal Community Controlled Health Services in communities across NSW with a high Aboriginal population will be invited to participate in the study. Each Aboriginal Community Controlled Health Service will be required to nominate one Aboriginal dental assistant and a local school/s to participate. Each Aboriginal Community Controlled Health Service will be given a set of criteria to select a local school to participate in the fluoride varnish program. The criteria will include (i) school enrols at least 12% Aboriginal children, (ii) children at the school experience high levels of untreated dental caries, (iii) community water is non-fluoridated or children consume high levels of sugar-sweetened beverages, and (iv) school does not receive another fluoride varnish program. A 12% minimum enrolment of Aboriginal children was selected as this is four times the average population proportion of Aboriginal people in Australia [20]. Once a local school meets the selection criteria, the Aboriginal Community Controlled Health Service will engage with the school principal to seek consent to implement the program at the school.

### Study design

Each Aboriginal Community Controlled Health Service will nominate one Aboriginal dental assistant to participate in the program, who has already completed a Certificate III in Dental Assisting. Each dental assistant will need to successfully complete additional training to be able to apply the fluoride varnish. The further training will be administered through NSW TAFE (HLTOHC006 Apply Fluoride Varnish). Each dental assistant will also receive training on the fluoride varnish application protocol developed specifically for this study (Additional file 1). Each dental assistant will be required to review the Health Care Complaints Commission’s Code of Conduct for unregistered health professionals, which applies to non-registered health practitioners providing healthcare services in NSW [21].

The six dental assistants will need to provide two references, a ‘Working With Children Check’ from NSW and a National Police Check from the Australian Federal Police. References and relevant checks will be sighted by a fluoride varnish pilot project supervisor. Upon completion of this vetting process, the names of the six dental assistants will be forward to the Chief Health Officer for NSW for approval to legally apply fluoride varnish through an exemption under the *NSW Poisons and Therapeutic Goods Regulations Act 2008*.

### Sample size

This study aims to recruit 500 Aboriginal children which constitute approximately 1% of all Aboriginal children enrolled in public schools in NSW [22]. Furthermore, six Aboriginal Community Controlled Health Services across NSW will be invited to participate in the study representing 15% of all Aboriginal Community Controlled Health Services across NSW.

### Recruitment of participants

Each school must also agree to take an active role in managing the consent process to enrol children into the study. The school will be required to engage an Aboriginal Education Officer to liaise with Aboriginal families to explain the consent form and enrol children into the study. This approach will allow Aboriginal families to ask questions about the program and provide informed consent for their child to participate in the study and aims to increase student participation and retention.

### Inclusion and exclusion criteria

Aboriginal children aged 5–12 years will be eligible to participate in the study. Inclusion of non-Aboriginal children will be allowed at the school’s request. Parents and/or guardians will be asked to complete a medical history questionnaire along with the consent form to ascertain each child’s asthma and allergy status. Children with uncontrolled asthma and a history of allergy to resins will be excluded [23].

### Description of intervention

Four days over the 12-month study period will be scheduled with the school for each dental assistant to apply the fluoride varnish to all eligible children. These days are known as ‘fluoride varnish days’. One ‘fluoride varnish day’ will take place each school term, and days must be at least 3 months apart. One further day will be scheduled 1 week after each ‘fluoride varnish day’ to follow up children who were absent. Those absent on the follow-up date will not receive a fluoride varnish application in that 3-month period.

Prior to the first fluoride varnish application by the dental assistant, a caries risk assessment developed specifically for this study will be completed by a supervising oral health therapist for each child with a valid consent form and no contraindicating medical history [Additional file 2]. Children who present with untreated dental caries will be referred to the local Aboriginal Community Controlled Health Service for dental treatment. Children identified as ‘at risk’ of developing dental caries will be enrolled into the study.

Duraphat fluoride varnish will be used as part of this study. Each fluoride varnish application will follow the protocol developed specifically for this study [Additional file 1]. Fluoride varnish applications will take place in a classroom with the child seated on a standard school chair. Teeth will be examined for visible plaque; if a substantial amount of plaque is present, children will be asked to clean their teeth with a toothbrush but no toothpaste. Teeth will be dried using one piece of gauze, and a thin film of 0.4 ml of Duraphat fluoride varnish [23] will be applied to the interproximal (in-between) and occlusal (chewing) surfaces of the teeth using a small brush. These surfaces are most susceptible to developing dental caries [24]. Fluoride varnish will be dispensed onto a 0.4-ml dispensing pad provided by the manufacturer, to ensure the correct amount is dispensed. Any residual fluoride varnish on the soft tissues of the mouth will be wiped off with a second piece of gauze. Each child will be given verbal post-operative instructions, as well as being issued with a sticker. Instructions will include abstention from food for 30 min and to resume toothbrushing normally in the evening. The sticker will note the time food consumption can resume. An oral health therapist will provide on-site supervision for the first fluoride varnish application and remote supervision for the remainder of the study period. In the unlikely event of an adverse reaction to the fluoride varnish, the child will discontinue enrolment in the study. Adverse reactions will be recorded in the ‘Fluoride varnish day’ summary sheet (Additional file 3). Figure 1 demonstrates the process flow of the proposed study.

**Fig. 1 Fig1:**
[figure not shown]
Process flow of the proposed study

### Data analysis

A process, impact and outcome evaluation will be undertaken based on the Quality Implementation Framework [25]. The process evaluation will include readiness and pre-training questionnaires for the dental assistants and supervising oral health therapists to determine the confidence of dental assistants applying fluoride varnish in the school setting. Impact measures will include the number of Aboriginal dental assistants and supervising oral health therapists participating in the study, satisfaction of key stakeholders to determine if schools are an appropriate setting for a fluoride varnish program and the acceptability of using dental assistants to deliver the program. Each fluoride varnish application will be recorded using a study-specific item number in the child’s confidential record stored in the local ACCHS’ dental software system. At the completion of the study, the item numbers related to the study and the demographics of each child will be extracted from each ACCHS’ dental software system. Descriptive analysis of fluoride varnish applications for all children included in the study will be performed using SAS Statistical software. The proportion of children who received one, two, three or four fluoride varnish applications over the study period will be presented with 95% CIs. This will determine whether this program can provide Aboriginal children at least three fluoride varnish applications over the 12-month study period. A cost analysis will also be undertaken to determine the overall cost-effectiveness of using dental assistants to apply fluoride varnish four times per year to school children compared to oral health therapists.

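### The varnish proportions are computed in all included children, who may include non-Aboriginal children, yet they are read as the answer for Aboriginal children

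*Protocol article*

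**What the plan says.** All references are to the protocol article.

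- **Background (objectives).** One secondary objective asks whether the model can give Aboriginal children three or more varnish applications within the 12 months.
- **Sample size.** The target counts Aboriginal children only: "This study aims to recruit 500 Aboriginal children".
- **Inclusion and exclusion criteria.** The core population is stated first: "Aboriginal children aged 5–12 years will be eligible to participate in the study". The next sentence widens it: "Inclusion of non-Aboriginal children will be allowed at the school’s request". No limit on number or share is given.
- **Data analysis, analysis set.** "Descriptive analysis of fluoride varnish applications for all children included in the study will be performed using SAS Statistical software".
- **Data analysis, statistic.** "The proportion of children who received one, two, three or four fluoride varnish applications over the study period will be presented with 95% CIs".
- **Data analysis, inference.** "This will determine whether this program can provide Aboriginal children at least three fluoride varnish applications over the 12-month study period".

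The same section says that each child's demographics will be extracted from the health services' dental software. It does not list the variables and plans no split by Aboriginal status.

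**The concern.** Consecutive sentences of the Data analysis section use two different populations. The analysis set and the reported proportion refer to children in general, while the conclusion drawn from them refers to Aboriginal children. The two coincide only if every included child is Aboriginal, and the eligibility section allows otherwise.

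This is more than a detail left to an analysis plan. The article names an analysis set and ties a conclusion to it, so an analysis plan that restricted the set to Aboriginal children would depart from the article as written.

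At stake is the one child-level proportion for which the article plans a confidence interval, and it answers a named objective. According to the Discussion, the pilot's results go to the Chief Health Officer in support of a scaling study. If delivery differs between the groups, for instance through attendance or retention, the pooled figure answers a different question. The non-Aboriginal share would be set by which schools ask, not by the design.

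**Working it through.** **What can be reproduced.** No stated figure bears directly on this point. The target of 500 is presented as about 1% of Aboriginal children in NSW public schools (implying 500 / 0.01 = 50,000). It does not come from a power or precision calculation, so there is no plan figure to re-derive.

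**Inputs**
- From the document: 500 Aboriginal children (Sample size) and a 95% confidence level (Data analysis).
- Assumed: pA = 60% of Aboriginal children receive at least three applications. The corresponding non-Aboriginal proportion pN is higher by 5, 10 or 20 points. Between 50 and 500 non-Aboriginal children are added. The documents give none of these values. A gap in the other direction reverses the sign of the shift.

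**Shift in the point estimate**

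With nN non-Aboriginal children, s = nN / (500 + nN).

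Pooled proportion = (1 − s) × pA + s × pN, so pooled − pA = s × (pN − pA).

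| nN | s | gap 5 points | gap 10 points | gap 20 points |
|---|---|---|---|---|
| 50 | 50/550 = 9.1% | 0.5 | 0.9 | 1.8 |
| 125 | 125/625 = 20% | 1.0 | 2.0 | 4.0 |
| 250 | 250/750 = 33.3% | 1.7 | 3.3 | 6.7 |
| 500 | 500/1000 = 50% | 2.5 | 5.0 | 10.0 |

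Shifts are in percentage points. Example: at s = 20% and a 20-point gap, 0.80 × 60 + 0.20 × 80 = 64%, against 60% in Aboriginal children.

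**Width of the interval when the groups do not differ**

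Wald half-width = 1.96 × √(p(1 − p)/n), ignoring clustering by school, at p = 0.60:
- 500 Aboriginal children alone: 1.96 × √(0.24/500) = 4.3 points.
- 625 pooled (s = 20%): 1.96 × √(0.24/625) = 3.8 points.
- 1,000 pooled (s = 50%): 1.96 × √(0.24/1000) = 3.0 points.

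With no gap the point estimate is unaffected, but the interval borrows its precision from children outside the population named in the conclusion.

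**Comparing the two effects.** At s of 20% or less, the shift is below or about equal to the half-width. It clearly exceeds the half-width only when both the share and the gap are large: 6.7 against 3.4 points at s = 33.3% with a 20-point gap, and 10.0 against 2.8 points at s = 50% with a 20-point gap.

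**Precision after the fix.** With the 500 targeted Aboriginal children, the half-width is 4.4, 4.3 or 4.0 points at p = 0.5, 0.6 or 0.7. The fix therefore needs no more children than are already planned.

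**The case against.** Several points on the other side have weight.

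- **It is conditional.** The mismatch arises only if a school asks. Nothing says that any will. The Abstract describes enrolling Aboriginal children, and Recruitment of participants describes an Aboriginal Education Officer liaising with Aboriginal families. If no school asks, the analysis set is already Aboriginal-only. This stands.
- **Pooling is partly inferred.** Describing all included children does not exclude a breakdown, and demographics are extracted. That makes a split probably feasible, but the article neither plans one nor names Aboriginal status among the variables.
- **Non-Aboriginal children may join the programme and not the study.** This is possible, but the sentence stands under the inclusion criteria, directly after the sentence on who may participate in the study. The plain reading is study inclusion.
- **An all-children figure has its uses.** The primary objective as worded in the Background refers to children at risk of caries in a school setting, and the cost analysis refers to school children. A programme-level delivery figure is legitimate for these. This stands, and it is a reason to keep that figure alongside the Aboriginal-child one.

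A reader might go further and infer from the 12% minimum Aboriginal enrolment in Setting that up to 88% of the children could be non-Aboriginal. With assumed rates of 60% and 80%, that would overstate delivery by 0.88 × 20 = 17.6 points. The documents do not support this. The 12% is an entry floor for a single school, not a forecast of the study mix. Applied study-wide alongside the 500 target, it would mean 500 / 0.12 = about 4,167 children. That is about 694 for each of six dental assistants, with one varnish day and one absentee day per term. It would also require every school to be at the floor and to ask, with equal uptake in both groups.

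**Conclusion.** The point holds in a limited form. As written, the article computes the application proportions in all included children, allows some of them to be non-Aboriginal, and reads the result as settling a question about Aboriginal children. The analysis set and the inference do not match whenever at least one school uses the option.

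The size is unknown. Under an assumed gap of 5 to 20 points, the shift is about 1 to 4 points at a 20% non-Aboriginal share and 2.5 to 10 points at 50%. It is zero if the groups do not differ. Even then the pooled interval is too narrow for an Aboriginal-child estimate: a half-width of 3.0 against 4.3 points at a 50% share, with p = 0.60 and clustering ignored.

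A reader might also infer that the result will be biased upwards, or that the study's main conclusion is compromised. Neither follows. The documents give no delivery rates for either group, so the direction is open. The question affected is a secondary objective of a single-group descriptive pilot with no stated success threshold.

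**What to change.** In Data analysis, state that the proportions with one to four applications, their 95% CIs and the at-least-three conclusion are computed in Aboriginal children. Report delivery to non-Aboriginal children, or to all children, separately and label it as a programme-level figure. Confirm that Aboriginal status is among the demographics extracted from the dental software, since the variables are not listed.

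The target of 500 needs no change, because Sample size already counts Aboriginal children only.

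The cost is one sentence of analysis wording and one filter, with no new data collection provided Aboriginal status is already recorded. If non-Aboriginal children are included, the main estimate will rest on fewer children and have a somewhat wider interval than one based on all treated children.

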An exemption has been sought from the Chief Health Officer for NSW under the *Poisons and Therapeutic Goods Regulations Act 2008*, to legally enable dental assistants to apply fluoride varnish in this pilot study. This pilot will be evaluated to determine the feasibility of utilising dental assistants to apply fluoride varnish at 3-monthly intervals in the school setting. The results of this pilot will be reported to the Chief Health Officer for NSW to propose the development of a scaling study to include an additional ten schools to determine if this approach is effective at scale. The development of a state or national model which would legally enable dental assistants to apply fluoride varnish four times per year in schools may increase the sustainability and scalability of fluoride varnish programs and improve the oral health of Aboriginal children in Australia.

This study protocol presents a process for Aboriginal dental assistants to apply fluoride varnish four times per year to Aboriginal school children in communities with a high Aboriginal population. The proposed pilot project aims to determine the efficacy of this approach and establish new, sustainable and scalable ways to enhance public oral health. Dental disease is largely preventable, and low-cost efficacious programs are critical to reducing the burden of disease in vulnerable populations.

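### The cost analysis can support a modelled cost comparison with therapist delivery, but the single-group design cannot determine comparative cost-effectiveness or efficacy

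*Protocol article*

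**What the plan says.** The last secondary objective in the Background is to determine "the cost-effectiveness of utilising dental assistants to provide four fluoride varnish applications in the school setting", relative to oral health therapists. The Data analysis section gives the method: "A cost analysis will also be undertaken to determine the overall cost-effectiveness of using dental assistants to apply fluoride varnish four times per year". The same sentence names oral health therapists as the comparator. The closing paragraph of the Discussion goes further: "The proposed pilot project aims to determine the efficacy of this approach".

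The design behind these aims is a "single group study across seven schools". On delivery, the abstract says: "Fluoride varnish (Duraphat) will be applied at 3-month intervals by the dental assistants to the teeth using a small brush". Under Description of intervention, therapists have two roles. They complete a caries risk assessment for each consented child before the first application, and they supervise: "An oral health therapist will provide on-site supervision for the first fluoride varnish application and remote supervision for the remainder of the study period". The Data analysis section says that study item numbers and demographics will be extracted at the end. It plans to report the proportions of children who received one, two, three or four applications, with 95% confidence intervals.

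**The concern.** Cost-effectiveness of one workforce against another concerns two differences, in cost and in effect. Efficacy concerns a health outcome set against what would have happened otherwise. The article states both aims with the verb *determine*, yet the study observes one workforce and counts applications.

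The Discussion says the results go to the Chief Health Officer for NSW to support a proposal for a scaling study in ten more schools, within an argument for a state or national model. A cost result presented as a finding of cost-effectiveness could carry more weight there than an assumption of equal effect can bear. Two features of the costing also need fixing in advance: whether cost is expressed at a nominal four applications or at those delivered, and where therapist time is charged.

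**Working it through.** The article gives no cost, effect or power figure for this comparison, so there is nothing to reproduce. The check sets each aim against the data described and then illustrates the costing choices.

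**1. Aims against data**

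| Aim | What it needs | What the article describes |
|---|---|---|
| Cost-effectiveness against therapists | Cost and effect under both models | Applications delivered by assistants; a cost analysis; no therapist-delivered group and no named external source |
| Efficacy | A later health outcome and a comparison | One caries risk assessment before the first application; no follow-up caries measure; no control |

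**2. The quantity that is missing**

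Write C for cost, E for effect, A for assistants and T for therapists. The incremental ratio is (C_A − C_T) / (E_A − E_T). The study can observe C_A, and E_A if effect means applications delivered or children reaching three. It observes neither C_T nor E_T. If E_A = E_T is assumed, the denominator is zero and only the cost difference C_A − C_T remains. That is cost minimisation, with C_T taken from a costed scenario.

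**3. Sample size does not help**

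With 500 children and an assumed 70% reaching three applications, the 95% half-width is 1.96 × √(0.7 × 0.3 / 500) = 0.040, or 4.0 points. Assume six equal clusters (500/6 = 83.3 children each) and an intracluster correlation of 0.01 to 0.10, which the article does not give. The design effect is then 1 + 82.3 × 0.01 = 1.82 up to 1 + 82.3 × 0.10 = 9.23, and the half-width is 5.4 to 12.2 points. This is the precision of a one-group delivery proportion. No value of n turns it into a contrast with therapists or a change in caries.

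**4. Nominal four against delivered applications (illustration only)**

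If every cost were fixed per round and children averaged three of four applications, cost per delivered application would be 4/3 = 1.33 times the nominal figure. With equal coverage the same factor applies to both models and their ratio is unchanged. It matters for the absolute cost, and for the comparison only if coverage differs.

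**5. Supervision (illustration only)**

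Let r be the assistant's hourly cost as a fraction of the therapist's. The values of r are assumptions. Relative labour cost is r plus the share of sessions with a therapist on site.

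| Reading of on-site supervision | Formula | r = 0.50 | r = 0.60 | r = 0.75 |
|---|---|---|---|---|
| Start-up cost, shown separately | r | 0.50 | 0.60 | 0.75 |
| One of eight scheduled days (four plus four follow-up) | (8r + 1)/8 | 0.625 | 0.725 | 0.875 |
| One of four rounds | (4r + 1)/4 | 0.75 | 0.85 | 1.00 |

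At r = 0.60 the apparent labour saving is 40%, 27.5% or 15% according to the allocation, before remote supervision is counted.

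**6. Equal coverage**

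If cost per enrolled child has ratio R = C_A/C_T, and p_A and p_T are the proportions reaching three applications, the ratio of cost per child reaching three is R × p_T/p_A. At R = 0.85 (one cell of the table above, treated here as total cost) the two models tie when p_A/p_T = 0.85. The conclusion therefore depends on p_T, which the study does not observe.

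**The case against.** The strongest reply is that an economic comparison needs no trial arm for the comparator. It can use a costed scenario or outside data. The Background describes an earlier small-scale study in which oral health therapists gave 3-monthly varnish and which provided at least three applications over 12 months. Applications delivered is a usable effect unit, and the pilot measures it. The article also treats the caries effect of varnish as established by meta-analysis, so comparing workforces need not require a new caries endpoint. Costing detail may sit in a fuller plan.

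Much of this stands. A reader might infer that no valid cost comparison is possible, and that would be wrong. What does not stand is the verb. The earlier study is cited as background and not named as the comparator. Equal effect would be an assumption or an unadjusted historical contrast. No analysis plan can recover a therapist effect or a caries outcome that the study does not collect.

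Four further readings are tempting and unsupported:

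- That the study expects fewer than four applications. Four days with follow-up days are scheduled, and at least three is a threshold, not a forecast.
- That the costing will leave out therapist time. The article does not say so.
- That the risk assessment belongs only to the assistant model. It is done once per child, and a therapist-delivered programme with the same entry step would need it too.
- That efficacy results will be reported to the Chief Health Officer. No efficacy analysis is planned. The abstract, the objectives and other parts of the Discussion speak of feasibility and acceptability, so the efficacy sentence may be loose wording.

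**Conclusion.** The point holds as a mismatch between stated aims and stated design. The study supports a modelled cost comparison under an explicit assumption of equal effect. It does not support a determination of cost-effectiveness against therapists, or of efficacy.

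This rests on the article's own description: one group, delivery by assistants only, caries status looked at only before the first application, and end-of-study extraction limited to item numbers and demographics. It does not rest on the illustrative figures. Those depend on assumed wage ratios, on costs fixed per round and on charging first-application supervision within a single year. They show that allocation can matter, not that the plan's result will be biased by any stated amount.

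The severity is moderate. One of five secondary objectives and one Discussion sentence are affected. The primary objective, recruitment and delivery analysis are untouched.

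**What to change.** - **Objective and Data analysis sentence.** Restate both as a modelled cost comparison of assistant delivery with therapist delivery (cost minimisation under a stated equal-effect assumption). Do not present cost-effectiveness as a conclusion.
- **Units.** Report observed cost per application delivered and per Aboriginal child receiving at least three applications, rather than cost at a nominal four.
- **Comparator.** Set this against a costed therapist scenario for the same visits, name the source of its inputs, and vary the equal-coverage assumption.
- **Therapist hours.** Log them prospectively. Charge on-site and remote supervision to the assistant model, with start-up supervision shown separately. Charge the initial risk assessment to both models where both would need it.
- **Discussion.** Replace efficacy with feasibility and acceptability in the closing paragraph.

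The cost is rewording, a small amount of time logging and a more modest economic claim. No change to design, sample size or delivery is needed.
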